| 1. **Data/ Statistical Analysis**   *1. Estimate the incidence of i) GP consultations for infection and ii) antibiotic prescriptions*  For every patient in cohort 1, data on all consultations for infection and antibiotic prescriptions occurring within the study period will be extracted. We will estimate the incidence of GP consultations for infection and antibiotic prescriptions. This will be done for all consultations and prescriptions, and then separately for each category of infection and each class of antibiotics, based on chapter 5.1 of the British National Formulary (BNF) (see Appendix Tables 1 & 2). The denominator will be estimated as total person-time contributed by patients in the cohort during the study period. We will use Poisson regression to estimate the adjusted rate of consultation and prescription, taking account of the effect of age, gender, SES, ethnicity, selected co-morbidity, smoking and obesity. Random effects will be included to take account of clustering of observations by practice. Rates will be assessed for overdispersion by additionally fitting a negative binomial model and testing for alpha greater than zero via a likelihood-ratio test. If rates are found to be overdispersed, the negative binomial model will be used instead of a Poisson model. Adjusted rate ratios will be presented with 95%-confidence intervals.  *2. Describe antibiotic prescribing patterns linked to the reason for prescription*  The overall number of antibiotic prescribing episodes will be calculated for each patient individually, counting all recorded prescriptions between 1st April 2007 and 31st December 2015. For each episode, a clinical indication will be ascertained. Read codes for a diagnosis or symptom of infection recorded on the same day as the antibiotic prescription will be assumed to represent an indication for the prescription. Where more than one possible indication within the same type of infection is recorded on the day of prescription, the more granular code will be used. If multiple indications across different types of infection are recorded, the prescription will be labelled as having multiple indications. Conversely, if no infectious indication for a prescription was found, the prescription will be labelled as having no infectious indication and we will look for any non-infectious codes associated with the date of antibiotic prescription. The ten most common indications will be established and compared to the same numbers for the period from 1998-2001.14 This approach will be replicated for each class of antibiotics based on chapter 5.1 of the BNF. Patterns of repeat consultation or prescription during episodes of infection which may be prolonged will be investigated for each antibiotic prescription extracted in objective 1. We will define a new episode as a consultation or prescription recorded at least 28 days after any previous consultation for infection or antibiotic prescription. We will undertake sensitivity analyses to investigate the impact of using different time periods to define an episode. We will also examine the use of regular (prophylactic) antibiotic treatment.  Proportions and appropriate 95%-confidence intervals will be calculated and all results will be stratified by age-group, gender, SES, ethnicity, selected co-morbidity, obesity and smoking status. Descriptive data will be displayed graphically.  *3. Estimate the incidence of adverse outcomes in the following 28 days*  For each of the selected clinical infection syndromes in the nested cohort study, events in CPRD, HES and ONS will be searched for all adverse outcomes of interest (see *M.* Exposures, Health Outcomes§ and Covariates). Crude incidence rates of for each outcome will be calculated for patients who were treated (exposed) and not treated (unexposed) with an antibiotic. The denominator will be estimated as the total person-time contributed by patients at risk of each adverse outcome, taking account of the fact that this will be different for each outcome. For example, exposed and unexposed patients cannot consult General Practice if they have been admitted to hospital and should therefore not contribute to the denominator during this period when estimating rates of GP re-consultation in the 28 days following consultation for infection. A Poisson regression model will be used to estimate adjusted rates of adverse outcomes in each group, controlling for age, gender, socio-economic status, ethnicity, co-morbidity, obesity and smoking status and assessing for interaction between age and co-morbidity. Random effects will be included to take account of clustering of observations by practice. If the outcomes are overdispersed, negative binomial models will be used instead of Poisson models. Adjusted rate ratios will be presented with 95%-confidence intervals.  *4. Estimate the number of patients needed to treat with antibiotics to avoid one infection-related adverse outcome*  For each clinical infection syndrome-related adverse outcome identified in objective 3, the odds of that outcome in the 28 days following consultation for those treated with antibiotics (unexposed) and not treated with antibiotics (exposed) will be estimated using logistic regression. We will calculate adjusted odds ratios for the protective effect of antibiotics, adjusting for age, gender, SES, ethnicity, year/season, co-morbidity and the probability of receiving antibiotic treatment (see *O. Plan for addressing confounding*) and assessing for interactions with age and co-morbidity. We will use mixed models to adjust for clustering at a practice level and to take account of clustering of observations within a patient due to repeat episodes of infection. Where there is a significant effect of antibiotics between treated and untreated patients, the NNT or NNH to prevent one individual from developing an adverse outcome is calculated as *1/(absolute risk difference)*. A significant effect will be defined by a p-value < 0.05 for the coefficients of antibiotic treatment and its interactions. To avoid an arbitrary cut-off point, p-values close to 0.05 will also be assessed but discussed separately. The NNT will then be used to assess the clinical relevance of any significant differences found. Whilst the relative risk reduction (RRR) may be similar, the NNT may be different due to differing background risk. This will be explored.  *5. Develop risk prediction tools to support clinical decision making*  For each cohort (i.e. for each of the clinical syndromes of UTI, RTI and SSTI), we will develop a logistic regression risk model to predict the risk of adverse outcomes if patients are treated versus not treated with antibiotics. Models will be developed on a random sample of 80% of the observations within a cohort, reserving 20% of the data to estimate the model’s predictive performance.  A negative outcome will be defined as the occurrence of any of the following within 28 days following the index consultation: hospital admission for infection or complication; re-consultation for infection; A&E admission; death. Antibiotic treatment will be defined as a prescription of an antibiotic on the day of consultation for clinical syndrome. Risk factors will be selected based on the analyses outlined in objectives 1-4 and broadly grouped into: socio-demographic variables, co-morbidity and clinical presentation. Biologically plausible interactions between risk factors and age and between risk factors and co-morbidities will be examined.  Whereas age and sex will be forced into the model, other risk factors will be added in order of their significance in objective 4. Risk factors will be kept in the model if they improve the predictive performance of the model as defined by model discrimination and model calibration.17 For example, a risk factor will be used in the model if it improves discrimination and/or calibration. If a variable improves discrimination but reduces calibration, it will still be included in the model, but will be omitted if it increases calibration at the cost of discrimination.  Model discrimination, i.e. the model’s ability to correctly identify patients with and without an outcome, will be estimated using the concordance (c) statistic.18 The c statistic represents the probability that between two randomly chosen patients, one with the outcome and one without, the model assigns a higher score to the patient with the outcome. As a second measure, model calibration will be assessed using the Hosmer-Lemeshow test.18 We will additionally assess model calibration graphically for reasons for poor calibration by comparing the mean observed outcome in deciles of predicted risk. In this calibration plot, the intercept indicates the extent to which predictions are systematically too low or too high, while the slope reflects overfitting of the model.  For each model, we will estimate the internal validity of discrimination and calibration estimates using cross-validation with bootstrap subsampling based on 1000 iterations. In a secondary analysis, we will assess model performance in subgroups by age, sex and co-morbidity.  Finally, we will develop a simplified scoring system using the risk factors in the model,17 assigning the total score to a specific absolute risk of adverse outcomes in the 28 days following consultation, comparing outcomes if an individual is treated versus not treated with antibiotics. We will assess the predictive performance of the risk scores using the approaches outlined above. |

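### Step 5 leads its calibration assessment with the Hosmer-Lemeshow test, whose result depends heavily on sample size and shows neither the size nor the direction of error; the planned intercept, slope and plot should lead instead.

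*Protocol*

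**What the plan says.** The point concerns the protocol, section N (Data/Statistical Analysis), step 5, on the risk prediction tools.

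- **Formal measure.** Discrimination is measured by the c statistic. Then: "As a second measure, model calibration will be assessed using the Hosmer-Lemeshow test". No significance level, number of groups or decision rule is given for the test.
- **Supporting measure.** "We will additionally assess model calibration graphically for reasons for poor calibration by comparing the mean observed outcome in deciles of predicted risk". For that plot, "the intercept indicates the extent to which predictions are systematically too low or too high, while the slope reflects overfitting of the model". Neither quantity is given a confidence interval or an acceptable range.
- **Where calibration is used.** Predictors stay in if they "improve the predictive performance of the model as defined by model discrimination and model calibration"; as an example, "a risk factor will be used in the model if it improves discrimination and/or calibration". Discrimination has precedence: "If a variable improves discrimination but reduces calibration, it will still be included in the model". The rule does not name a calibration measure.
- **Subgroups and score.** In a secondary analysis "we will assess model performance in subgroups by age, sex and co-morbidity", again with no measure named. The simplified score is to be evaluated by the same approaches as the model.
- **Data.** Models are built on a random 80% of observations, "reserving 20% of the data" for performance. Discrimination and calibration estimates are also to be validated internally with 1000 bootstrap iterations.

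**The concern.** The tool gives a patient an absolute risk with and without an antibiotic. Its calibration is therefore a question of size: by how much, and in which direction, are the risks wrong? The Hosmer-Lemeshow test asks whether the fit is exact. For a fixed error its statistic grows in proportion to the number of episodes, and it returns only a p-value.

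The validation sets here range from hundreds of thousands of episodes to perhaps a few thousand or fewer in a co-morbidity subgroup. The same relative error could be flagged in the RTI cohort, be a coin toss in the UTI cohort and go unnoticed in a small subgroup. Whether co-morbid patients differ is the study's central question, so the small subgroups matter. The test also assumes independent observations, whereas section K lets a patient enter a cohort more than once, and patients are clustered in practices.

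**Working it through.** **Inputs from the protocol.** Section I gives 3,355,353 respiratory cases and puts urinary and skin infections at 1/5 and 2/5 of that. 3,355,353/5 = 671,070.6 and 2 × 3,355,353/5 = 1,342,141.2, which reproduces the stated 671,070 and 1,342,141. The 20% hold-outs are then 671,071 (RTI), 268,428 (skin) and 134,214 (UTI). Section I expects an outcome risk of about 2.4%. The protocol states no calibration figure that could be reproduced.

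**Assumptions.** Test level 0.05; 8 degrees of freedom (10 shown as a check); independent episodes; true risk a factor (1 + d) times the predicted risk throughout. A risk of 10% is shown as an alternative, because the composite in step 5 includes re-consultation.

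**Formula.** The statistic is approximately non-central chi-square with non-centrality λ = N·d²·p/(1 − p). Power is the probability of exceeding the 95% point of the central distribution.

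**Whole hold-outs, d = 5%, p = 2.4%** (error 0.05 × 2.4 = 0.12 points). Here p/(1 − p) = 0.02459.

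| Cohort | λ | Power, 8 df | Power, 10 df |
|---|---|---|---|
| RTI | 41.25 | 0.999 | 0.999 |
| Skin | 16.50 | 0.84 | 0.81 |
| UTI | 8.25 | 0.49 | 0.45 |

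Letting predicted risks vary between patients (logit-normal, SD 0.8, 10 df) gives 0.999, 0.82 and 0.46.

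**Sensitivity to the error chosen, d = 3%, 8 df.** At 2.4% risk (0.07 points): 0.79, 0.35 and 0.18. At 10% risk (0.3 points): 1.00, 0.98 and 0.74.

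**Subgroups.** The protocol gives no subgroup sizes within the cohorts. Section H reports 36,119 COPD patients, the smallest listed group, in an earlier three-year study. Assuming one RTI episode each, 20% is about 7,200 episodes. Assuming also the 1/5 ratio for UTI, about 1,400.

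| Episodes | Risk | d | λ | Power, 8 df |
|---|---|---|---|---|
| 1,400 | 2.4% | 20% | 1.38 | 0.10 |
| 7,200 | 2.4% | 20% | 7.08 | 0.42 |
| 1,400 | 10% | 20% | 6.22 | 0.37 |
| 7,200 | 10% | 20% | 32.0 | 0.99 |
| 1,400 | 2.4% | 50% | 8.61 | 0.51 |
| 7,200 | 2.4% | 50% | 44.3 | 1.00 |

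**What the intercept would do on the same data.** A one-degree-of-freedom comparison of observed with expected events has z = √λ. At 2.4% risk and d = 20%, z = 2.66 and power is 0.76 with 7,200 episodes (against 0.42); z = 1.17 and power is 0.22 with 1,400 (against 0.10). The approximate 95% half-width of the observed/expected ratio near 1 is 1.96·√[(1 − p)/(N·p)]. At 2.4% risk this is 1.5% (RTI), 2.4% (skin), 3.4% (UTI), 15% (7,200 episodes) and 33% (1,400 episodes). The interval shows directly what the data can and cannot exclude; the p-value does not.

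**Clustering.** As an illustration, if dependence inflated the statistic by an assumed factor of 1.2 to 1.5, a perfectly calibrated model would be rejected 11% to 24% of the time instead of 5% (8 df).

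**The case against.** The strongest reply is that the protocol does not rely on the test alone. The plot by decile, the intercept and the slope are in the same paragraph, and a trivial rejection in 671,000 episodes would look trivial on that plot. This stands, and it makes the remedy a change of emphasis plus intervals. It does not justify leading with the test, because the plot is presented as a way to find reasons for poor calibration.

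Three stronger readings are tempting, and the document does not support them.

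- **A reader might infer that p > 0.05 passes a model or subgroup and p < 0.05 fails it.** That is the usual reading of the test, but the protocol writes no such rule. Nor does it name the test in the subgroup sentence or the retention rule.
- **A reader might infer that badly miscalibrated subgroups would escape.** At these sizes a 50% error is mostly detected; the exception is the smallest UTI-type subgroup at 2.4% risk (power about 0.5). In larger RTI groups even a 20% error at 2.4% risk is usually found: 0.82 for CKD (20% of 79,056) and 0.93 for diabetes (20% of 107,382), again assuming one episode per patient.
- **A reader might infer that all three cohorts fail for trivial errors.** A 3% error at 2.4% risk is rejected only 35% (skin) and 18% (UTI) of the time.

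It can also be said that intervals and clustered standard errors belong in an analysis plan, which is not at hand. That is fair for their detail. The choice of the test as the formal measure is made in the protocol itself.

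**Conclusion.** The point holds as a poorly chosen lead measure, not as a flaw that invalidates step 5. The only formal calibration measure named gives neither size nor direction of error for a tool that outputs absolute risks. Its result changes with N for a fixed error: about 0.999, 0.84 and 0.49 across the three hold-outs for a 0.12-point error at 2.4% risk. In small subgroups moderate errors of 20% are often missed at 2.4% risk (58% of the time with 7,200 episodes, 90% with 1,400).

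The hold-out sizes and the 2.4% follow from the protocol. The subgroup sizes, the 10% risk, the 0.05 level, the degrees of freedom and independence are assumptions. If the composite risk is nearer 10%, the subgroup problem shrinks to the smallest groups and the large-cohort problem grows. This is a cheap improvement.

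**What to change.** In section N, step 5:

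1. Drop the Hosmer-Lemeshow p-value as the calibration measure.
2. Make the calibration intercept (or observed/expected ratio), the slope and the plot the primary measures for the model, the simplified score and the subgroups. Report them separately for treated and untreated patients, with 95% confidence intervals that allow for clustering by patient and practice.
3. State that these measures are meant wherever calibration enters the predictor-retention rule.
4. Report a subgroup whose interval is wide as calibration not established, and set beforehand what counts as wide.

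The cost is a few sentences of text and a little more analysis on predictions that will exist anyway. The downside is that some small subgroups will be reported as inconclusive, more so once they are split by treatment.

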| 1. **Technical Summary (Max. 200 words**)**§**   **§***Please note:**This information will be published on CPRD’s website as part of its transparency policy*  Antibiotic overuse drives antimicrobial resistance. In primary care rates of antibiotic prescribing vary widely, associated with characteristics of the patient and GP prescribing behaviour.  The aim of this study is to investigate whether analyses of patient level characteristics can guide antibiotic prescribing decisions in primary care.  Using data from patients who contributed to CPRD between April 2007 and December 2015, we will describe the diagnosis, antibiotic treatment and clinical outcomes of patients with common infection syndromes. These analyses will be stratified by patient characteristics including: age, gender, social deprivation, selected co-morbidities, obesity and smoking.  In a series of cohort studies of patients with common infection syndromes, we will: a) estimate the rate of adverse outcomes comparing those who were treated with antibiotics to those who were not, using Poisson regression and b) calculate the number needed to treat to avoid one infection related adverse outcome using multi-level logistic regression, taking account of patient’s vulnerability through the use of propensity scores. These analyses will be stratified by each of the patient characteristics listed above. This work will be synthesized through models that predict each patient’s risk of adverse outcomes, comparing the scenario of antibiotic treatment versus no antibiotic treatment. |

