| 1. **Objectives, Specific Aims and Rationale**   *Objective*  To investigate the use of antibiotics and their protective effect against complications of infection to inform the development of risk prediction models to guide antibiotic treatment decisions for suspected infection in primary care.  *Aims*   1. Estimate the incidence of i) GP consultations for infection and ii) antibiotic prescriptions by: age-group, gender, SES, ethnicity, selected co-morbidities, obesity and smoking status 2. Describe antibiotic prescribing patterns linked to the reason for the prescription by: age-group, gender, SES, ethnicity, selected co-morbidities, obesity and smoking status 3. Estimate the incidence of adverse outcomes in the following 28 days including: hospital admission for infection; A&E admission; re-consultation for infection; re-consultation for antibiotic side-effects (rash, nausea, …) and death for patients with a GP consultation for i) respiratory tract infection ii) urinary tract iii) skin/soft tissue infection, comparing patients with each listed age/co-morbidity group (including smoking status and obesity) to non-comorbid patients 4. Estimate the number of patients needed to treat with antibiotics to avoid one infection-related adverse outcome, comparing the results for each age/co-morbidity group to non-comorbid patients 5. Develop risk prediction tools to support clinical decision making and communication with patients   *Rational*  We have previously shown that more than half of all antibiotic prescriptions in primary care are issued to less than 10% of patients, and that this 10% of patients have high levels of co-morbidity.1 Targeting such high-frequency users of antibiotics in antimicrobial stewardship programmes might provide opportunities for a more effective intervention approach. Underlying this hypothesis is the assumption that it might be safe and feasible to reduce prescribing in patients with the highest levels of antibiotic prescribing, many of whom have co-morbidity.  To investigate whether higher rates of antibiotic use are likely to be justified in higher risk patients compared to patients who lack these risk factors, we will undertake a series of studies to investigate which patients in terms of age, gender, SES, ethnicity, selected co-morbidities, obesity and smoking get the most antibiotics. We will determine which patients are most likely to receive antibiotics for which infections and relate this to national guidance on antibiotic prescribing. To estimate whether the protective effect of antibiotics differs according to the patient’s age and the presence of co-morbidity, obesity or their smoking status, we will estimate the risk of infection related adverse-outcomes, comparing patients who have been treated with antibiotics to those who have not been treated with antibiotics for each of these groups. We will use these estimates to calculate the number of patients who need to be treated with antibiotics to avoid one infection-related adverse outcome (NNT), accounting for age, gender, SES, ethnicity, co-morbidity, obesity and smoking status. This will inform the development and validation of individualised risk-prediction models to support clinical decision-making and patient communication around the need for antibiotic treatment for suspected infection in primary care. |

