| 1. **Exposures, Health Outcomes§ and Covariates**   **§***Please note:**Summary information on health outcomes (as included on the ISAC application form above) will be published on CPRD’s website as part of its transparency policy*  *Exposure*  Exposures will include i) prescription of an antibiotic ii) GP consultation for suspected infection (see Appendices: Table 1 – Codelist for antibiotics, Table 2 – Codelist categorising indications for antibiotic use and Table 3 – Codelists to identify patients with suspected respiratory tract, urinary tract or skin/soft tissue infection)  *Health Outcomes*  The following outcomes (within 28 days of presentation in primary care) will be separately considered for analysis:   - Re-consultation for the same type of infection (CPRD; see Appendix Table 3) - Re-consultation for a side effect of antibiotic treatment (CPRD; see Appendix Table 4a –side effects of antibiotic treatment) - Complications of infection in primary or secondary care (CPRD and inpatient HES; see Appendices: Table 4b and 4c – complications of infection; depending on the indication) - Admission to Accident & Emergency (HES A&E) - All-cause hospitalisation (inpatient HES) - All-cause mortality (CPRD, HES and ONS)   We will undertake a sensitivity analysis to investigate the impact of excluding outcomes that occur on the same day as the exposure. The impact of different time windows will be explored, informed by a literature review on the natural history of the duration of different infections.  *Covariates*  We will include the following covariates:   - Age (classified as 0-4, 5-17, 18-44, 45-64, 65-84, 85-94 and 95+, years of age inclusive) - Sex (female and male) - Index of Multiple Deprivation (IMD; 1-5) - Co-morbidities (coded as indicator variables based on national guidance from Public Health England3 and feasibility1; see Appendix Table 5 for comorbidity code list)   - Diabetes   - Chronic Kidney Disease (CKD)   - Chronic Obstructive Pulmonary Disease (COPD)   - Asthma - Obesity - Smoking status15 - Season (months or quarters) and year - Ethnicity   We will undertake a sensitivity analysis of the impact of coding co-morbidities as binary indicator variable and as total number of co-morbidities. |

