| 1. **Plan for addressing confounding**   In objectives 1-3 the aim is to describe rates and undertake descriptive analyses rather than to make inferences about the effect of antibiotic treatment, which is the purpose of objectives 4 and 5. For this reason the issue of confounding is only relevant to objectives 4 and 5.  Individuals who are at higher risk of complications will be more likely to be prescribed antibiotics by their GP (i.e. confounding by indication), introducing a systematic difference between those who are treated and not treated with antibiotics. In this scenario, untreated cases will be less likely to experience adverse events irrespective of their exposure to antibiotics, tending to underestimate the protective effect of antibiotics. We will use propensity score methods to attempt to adjust for this issue. These methods are increasingly used to mitigate the consequences of non-random allocation of treatment in observational studies by modelling the a priori probability of each patient to receive the treatment.  We will use the treatment propensity scores to perform an inverse probability of treatment weighting to account for baseline differences in treated and untreated participants. This will enable assessment of absolute risk and numbers needed to treat to prevent re-consultation and hospitalisation in different groups.19 Propensity score weighting in effect produces a synthetic sample in which the distribution of measured baseline covariates is independent of treatment assignment. Presentation and analyses of results are very similar to a randomized trial allowing assessment of absolute risk and numbers needed to treat in different groups.  In order to create appropriate propensity scores, we will attempt to capture indicators for severity of disease and patients’ risk of complication, such as prior hospitalisation and immunosuppression. Measures such as vital signs are usually poorly recorded which can hamper efforts to estimate disease severity. To overcome this issue we will use GP prescribing preference as an instrumental variables, as described by Davies et al 2013.20  Besides confounding by indication, a number of further factors might influence prescribing. The decision to prescribe an antibiotic is a complex process, depending on multiple characteristics on the patient and practice level. Patients’ demographic factors, patients’ attitude towards antibiotic prescribing, physicians’ workload, date of consultation and geographic location of the practice have been found to influence physicians’ prescribing decisions.21 The use of further instrumental variables may help to estimate the impact of these factors in our analysis and we will also control for differences in prescribing habits between practices through the application of random effects models taking account of potential correlation within multiple episodes of the same patient and between patients within the same practice.  Acknowledging that differences in practice prescribing do not necessarily constitute actually differing prescribing habits but might instead reflect underlying differences in coding, we will undertake an exploratory analysis to look at variation between practices graphically. Using a novel approach we will visualise variability between multiple data-generating sources (i.e. practices) that was specifically designed and tested for multitype, multivariate and multimodal biomedical data.22,23 Where outlying practices are identified, analysis will be re-run without those practices and results presented with the analysis outlined in *N. Data/ Statistical Analysis*. |

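### Section O declares confounding irrelevant to objective 3, yet step 3 reads as an adjusted treated-versus-untreated comparison with no control for indication and no season or year in its model

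*Protocol*

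**What the plan says.** Section O gives this reason for limiting confounding control: "In objectives 1-3 the aim is to describe rates and undertake descriptive analyses rather than to make inferences about the effect of antibiotic treatment". It then concludes: "For this reason the issue of confounding is only relevant to objectives 4 and 5".

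Other sections describe objective 3 as follows.

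- The technical summary says the study will "estimate the rate of adverse outcomes comparing those who were treated with antibiotics to those who were not, using Poisson regression".
- Section G assigns to objective 3 the 28-day adverse outcome rates of patients with and without antibiotics.
- Section N, step 3, begins: "Crude incidence rates of for each outcome will be calculated for patients who were treated (exposed) and not treated (unexposed) with an antibiotic". It then fits a Poisson (or negative binomial) model for adjusted rates by group, "controlling for age, gender, socio-economic status, ethnicity, co-morbidity, obesity and smoking status and assessing for interaction between age and co-morbidity", with practice random effects. It ends: "Adjusted rate ratios will be presented with 95%-confidence intervals".
- Aim 3 in section D gives a different contrast: "comparing patients with each listed age/co-morbidity group (including smoking status and obesity) to non-comorbid patients". Section L also speaks of population subgroups for objectives 1 to 4 and names the treated/untreated comparison only for objective 4.

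Section M lists "Season (months or quarters) and year" among the covariates to be included and ties it to no particular objective. Step 4 adjusts for year/season and for the probability of being treated. Step 3 names neither.

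**The concern.** An adjusted ratio of exposed to unexposed patients with a confidence interval will be read as an effect estimate, whatever another section calls it. Directly after setting confounding aside for objective 3, section O explains that GPs are more likely to treat patients at higher risk, and that this makes antibiotics look less protective than they are. That mechanism belongs to the treated/untreated contrast itself. It does not begin at objective 4. The limitations section calls confounding by severity the major challenge of the study.

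At stake is a report with two adjusted antibiotic ratios for each syndrome and outcome over the same 28 days: a rate ratio from step 3 and an odds ratio from step 4. They would rest on different adjustment sets, and the plan itself expects the first to be biased.

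**Working it through.** The plan gives no figure on this point to reproduce. The check is a comparison of text, followed by an illustration of size.

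**Adjustment sets side by side**

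- Age, gender, SES, ethnicity and co-morbidity: named in both step 3 and step 4.
- Obesity and smoking: named in step 3, not named separately in step 4.
- Season and year: listed in section M and used in step 4, absent from step 3. Section G's list of factors for all steps omits them too.
- Probability of treatment: used in step 4, absent from step 3. Section O plans propensity weighting and a prescribing-preference instrument, but only for objectives 4 and 5.
- Extra covariates from the Amendments section (cardiovascular disease, liver disease, immunosuppression, Charlson index): added to the analysis generally. No season, year or propensity term is among them.

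Step 3 therefore controls for seven measured factors, and for more after the amendment, but not for indication or severity. Controlling for those seven is itself confounding control, so section O's sentence does not describe the analysis that section N plans.

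**Illustration of size**

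Take severity as one unmeasured binary confounder, unrelated to the adjusted factors and with the same effect in both groups:

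observed ratio = true ratio × [1 + p1(R − 1)] / [1 + p0(R − 1)]

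Here p1 and p0 are the shares with high severity among treated and untreated patients, and R is the rate ratio for high severity.

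Inputs: the true ratio of 0.69 is the average antibiotic odds ratio quoted in section I, used here as if it were a rate ratio. The values of p1, p0 and R are assumptions and are not in the protocol. Four pairs (p1, p0) were used: (0.2, 0.1), (0.3, 0.1), (0.4, 0.2) and (0.5, 0.2), with R from 1.5 to 4.

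- Smallest bias, (0.2, 0.1), R = 1.5: 1.10/1.05 = 1.048; 0.69 × 1.048 = 0.72.
- Intermediate, (0.4, 0.2), R = 2: 1.40/1.20 = 1.167; 0.69 × 1.167 = 0.81.
- Intermediate, (0.3, 0.1), R = 3: 1.60/1.20 = 1.333; 0.69 × 1.333 = 0.92.
- Largest bias, (0.5, 0.2), R = 4: 2.50/1.60 = 1.5625; 0.69 × 1.5625 = 1.08.

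The range of 0.72 to 1.08 belongs to these four pairs and not to every combination of the percentages. Equal severity in both groups gives no bias. Pairing 0.5 with 0.1 at R = 4 gives 2.50/1.30 = 1.923, and 0.69 × 1.923 = 1.33. The direction matches section O. The size depends on the inputs.

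**The case against.** The best defence is that the protocol disclaims the inference. Section O says objectives 1 to 3 only describe, section L keeps the treated/untreated comparison for objective 4, and Aim 3 defines the objective 3 contrast by age and co-morbidity. Step 3 does not say which contrast its rate ratios express. A descriptive step followed by a causal one is a legitimate design, and weighting step 3 like objective 4 would largely duplicate objective 4.

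Much of this stands. The contrast is not fixed unambiguously, and the stated descriptive aim limits how serious the point is. It does not remove the conflict, because the technical summary, section G and the exposed/unexposed labels in step 3 all point to treated versus untreated.

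Some stronger readings are tempting but not supported:

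- A reader might infer that objective 3 has no confounding control. It adjusts for seven factors, and the amendment adds more. The gap is indication and severity.
- A reader might infer that season and year are deliberately excluded. Section M includes them without restriction, so this is an inconsistency to reconcile.
- A reader might infer that the bias passes into the prediction models, because step 5 draws risk factors from objectives 1 to 4. But step 5 adds variables in order of their significance in objective 4 and keeps them on predictive performance. The antibiotic effect is estimated within the step 5 model.
- A reader might note that step 1 also omits season and that the study window holds unequal numbers of each quarter. Step 1 compares patient groups over shared calendar time, and an uneven count does not by itself bias those contrasts.
- A reader might set seasonal bias in step 3 against the detectable odds ratio of 0.975 in section I. That figure concerns the odds ratio estimated in step 4, which does adjust for year/season.

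**Conclusion.** The point holds in limited form. Section O's sentence conflicts with a step that, on the most natural reading, presents adjusted antibiotic rate ratios, and with section O's own account of confounding by indication. If the ratios are treated versus untreated, they lack control for indication and severity and are expected to understate protection. Under the assumed inputs, a 31% reduction (1 − 0.69) could appear as anything from a 28% reduction (1 − 0.72) to an 8% increase (1.08). The documents do not show that antibiotics will appear harmful; that needs the more extreme assumptions. If the ratios are co-morbidity contrasts, step 3 and the technical summary need to say so. Either way the text should be corrected before step 3 is reported.

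**What to change.** 1. Reword the section O sentence so that confounding applies to any comparison of treated with untreated patients, including one made under objective 3.
2. State in step 3 which contrast the adjusted rate ratios estimate, and bring the technical summary, Aim 3, section G and section L into line.
3. Then choose one of two routes. Either estimate the treated/untreated ratio with the objective 4 propensity weights plus season and year, or report treated and untreated rates as crude and descriptive only and keep adjusted rate ratios for the co-morbidity contrasts. The second route preserves the stated descriptive purpose and avoids duplicating objective 4.
4. Align the step 3 covariate list with section M on season and year.

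The cost is a wording change to the protocol. The weights and calendar variables are already planned for objective 4, so no new data are needed.
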